## Abstract

**Background:**

Obstructive sleep apnea (OSA) is a common sleep disorder, and in pregnancy, it is associated with an increased risk of complications, including gestational diabetes mellitus and preeclampsia. Supine sleep may worsen OSA, and in pregnancy, it is associated with an increased risk of stillbirth due to effects on fetomaternal blood flow. Continuous positive airway pressure (CPAP) therapy is considered the gold-standard treatment for moderate to severe OSA, although compliance is frequently poor; positional therapy (PT) is generally less effective than CPAP in nonpregnant patients but may be better tolerated and more accessible during pregnancy. There is limited data on whether widespread, early screening for sleep disorders in pregnant women with symptoms of sleep-disordered breathing or at high risk of metabolic complications and subsequent early intervention with CPAP or PT attenuates fetomaternal risks.

**Objective:**

This study aims to determine the feasibility of conducting a randomized controlled trial to assess improved fetomaternal outcomes in a high-risk pregnant population with OSA, using CPAP or PT, initiated by the 16th week of gestation.

**Methods:**

This study is a randomized, controlled, open-label feasibility study in which pregnant women with an apnea-hypopnea index (AHI) or respiratory disturbance index (RDI) ≥5 are treated with CPAP (auto-titrating and fixed pressure) or positional therapy from early gestation (by 16 weeks) until delivery. The primary outcome is the feasibility of the study protocol and the development of gestational diabetes mellitus by the 28-week gestation period. Secondary outcomes include the development of hypertensive disorders of pregnancy (HDP), maternal weight gain, uterine artery blood flow, glycemic control during pregnancy (in participants who develop gestational diabetes), changes in maternal circulating biomarkers, and neonatal birthweight complications. Polysomnography at 28- to 32-week gestation period, postpartum polysomnography, therapy compliance, and patient acceptability are also assessed.

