### Eligibility Criteria

Eligible participants are defined as women aged 18 years of age and older; in early pregnancy (up to 14-week gestation period); at increased risk of metabolic complications defined as one or more of (1) BMI greater than or equal to 35 kg/m^2^, (2) previous GDM, (3) previous personal history of preeclampsia (or in mother or sister), (4) underlying renal disease, (5) maternal type 2 diabetes (pregestational), and (6) symptoms of SDB including snoring, witnessed apnea, mild excessive daytime sleepiness (EDS; which does not meet the criteria for severe EDS defined by Epworth Sleepiness Scale (ESS>15), or a fall asleep accident, or near-miss accident in the previous 12 months), or tiredness; and obstructive sleep apnea diagnosed by polysomnography defined as RDI or AHI ≥ 5.

The participants will be excluded if they have (1) a previous diagnosis of OSA on active treatment, (2) confirmed GDM or preeclampsia, (3) maternal type 1 diabetes, (4) multifetal gestation, (5) known fetal chromosomal abnormality, (6) inability to provide informed consent, and (7) severe EDS based on clinical assessment (eg, including a fall asleep motor vehicle accident or near miss, transient sleepiness while driving or at lights or needing to pull over due to sleepiness while driving, or transient sleepiness in any other dangerous situation, ie, cooking, carrying a baby) or ESS of greater than 15.

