### Outcome Assessment

An oral glucose tolerance test will be undertaken for the assessment of gestational diabetes at 28 weeks (in addition to earlier testing if clinically requested). Collection of fasting blood will be followed by administration of 75 g oral glucose load, with 1 and 2 hours of blood collection. Interpretation will follow the Australasian Diabetes in Pregnancy Society (ADIPS) 2020 guidelines [38].

Blood pressure (BP) will be recorded at each study visit. Diagnosis of HDP will be defined as per the Society of Obstetric Medicine of Australia and New Zealand (SOMANZ) guidelines [39].

Anthropometric measurements (height, weight, and BMI) will be recorded during the randomization visit, and weight will be checked at subsequent study visits by study staff using hospital clinic scales.

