### Statistical Methods

This trial is a feasibility trial, and as such, no power calculations for the RCT were derived. We prespecified to assess the diagnostic accuracy of the home sleep tests as well as the screening questionnaires following the STARD (Standards for Reporting of Diagnostic Accuracy) guidelines. The accuracy will be assessed at various cutoff points using a receiver operating characteristic curve. The area under the receiver operating characteristic curve and positive and negative predictive values in the patient population will be derived. The first recruitment target will be 50 participants, which provides at least 80% power (α=.05) to detect a C-statistic of 0.7 when the allocation ratio is 1 (ie, 50% prevalence) and 0.75 when the allocation ratio is 2 (ie, 20% prevalence). We will be comparing Apnealink Air and SOMTE unattended PSG to attended PSG. Further exploratory analysis will be undertaken to assess whether any factors at booking, including the results of the sleep questionnaire, biomarkers, clinical factors, and history in combination with findings of unattended PSG, Apnealink, or attended PSG, are predictive of poor outcomes (either maternal or fetal, as discussed above). A composite of the combined adverse maternal outcomes and combined adverse fetal outcomes will also be assessed as an outcome. Data will be displayed as mean (SD), 95% CIs, and median (IQR) as appropriate based on data distribution. An intention-to-treat analysis will be undertaken for the primary outcome as well as the secondary outcomes. A per-protocol analysis (for primary and secondary outcomes) will also be undertaken, and both data will be presented. A *P* value of <.05 will be considered statistically significant. Where multiple analyses are undertaken, adjustments will be made for multiple comparisons. Longitudinal analysis of repeated measures will be undertaken where measurements are undertaken several times. Where differences at baseline exist between the groups, adjustments will be made statistically. Where less than 10% of any data point is missing, data will be imputed. We have preplanned an exploratory analysis of flow characteristics of all sleep tests to investigate sub-criterion flow changes related to long-term fetomaternal outcomes.

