This feasibility RCT will assist in the understanding of the maternal and health care system challenges in undertaking a CPAP intervention during pregnancy. The therapies in this study will commence by the 16th week of gestation and will be overseen by an experienced sleep therapist to improve CPAP and PT compliance. This is important as many clinical trials involving CPAP are limited by poor compliance of the participants. We will encourage compliance to interventions through an initial education session at randomization by the trial sleep therapist and at each study visit. At these visits, the participants will be provided feedback regarding their therapy compliance and efficacy, and through a series of questionnaires, we will assess barriers to therapy. We anticipate an improvement in fetomaternal outcomes such as improved blood pressure control, reduced incidence of GDM, and preeclampsia in the interventional groups with good adherence to therapy. The learnings from undertaking this work will be important for consideration when expanding to a larger trial. The results of the study will be published in peer-reviewed journals and presented at national and international conferences.

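### Glycemic control is defined only in women who develop GDM, a post-randomisation subgroup that treatment is expected to shrink, so a between-arm comparison there is not a randomised one

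*Protocol article*

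**What the plan says.** The Methods paragraph of the Abstract names among the secondary outcomes "glycemic control during pregnancy (in participants who develop gestational diabetes"). The same paragraph makes GDM a primary outcome: "The primary outcome is the feasibility of the study protocol and the development of gestational diabetes mellitus by the 28-week gestation period". Eligibility Criteria excludes women with "confirmed GDM or preeclampsia", so the GDM that defines the subgroup is diagnosed after entry. The Discussion (Principal Findings) anticipates "reduced incidence of GDM, and preeclampsia in the interventional groups with good adherence to therapy".

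On analysis, Statistical Methods states: "An intention-to-treat analysis will be undertaken for the primary outcome as well as the secondary outcomes". It adds a per-protocol analysis and a general rule that a P "value of <.05 will be considered statistically significant". It does not say how an outcome defined only in women with GDM fits these rules.

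On measurement, Outcome Assessment states: "An oral glucose tolerance test will be undertaken for the assessment of gestational diabetes at 28 weeks", and then: "Collection of fasting blood will be followed by administration of 75 g oral glucose load, with 1 and 2 hours of blood collection". No outcome listed in the article uses these glucose values as continuous measures. The article's list is open-ended, and the Methods section refers to the trial registry for all primary and secondary outcomes.

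**The concern.** Randomisation makes the three arms comparable at entry. It does not make the women who later develop GDM comparable across arms. If therapy changes who develops GDM, as the Discussion hopes, the women with GDM in a treated arm differ systematically from those in the control arm. Glycemic control among them then mixes two things: the effect of therapy on glucose, and the change in who is counted.

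Two things are at stake. First, a real benefit may be hidden or, under some mechanisms, appear as harm. Second, the trial exists to supply preliminary efficacy data for designing and powering a larger trial (Introduction). A difference taken from a small, selected subgroup is a poor basis for that, and the selection bias would persist in a larger trial that kept the same definition.

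**Working it through.** The article gives no figure for this outcome and no power calculation for the randomised comparison, so there is nothing to reproduce beyond 3 × 16 = 48, which agrees with Trial Design.

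**Inputs from the article.** 16 women per arm; GDM a primary outcome, absent at entry and expected to fall with treatment; significance threshold 0.05.

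**Assumptions.** Control-arm GDM risk *p* of 20%, 30% or 40%; glucose as one normal variable with SD 1; GDM defined as exceeding the cut-off *c* with P(Y > c) = *p*; two-sided testing and 80% power.

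**1. Subgroup size.** Expected number per arm is 16*p*: 16 × 0.20 = 3.2; 16 × 0.30 = 4.8; 16 × 0.40 = 6.4. At 20%, the chance of at most one case in an arm is 0.8^16 + 16 × 0.2 × 0.8^15 = 0.141. The chance that at least one of three arms has fewer than two cases is 1 − (1 − 0.141)^3 = 0.37. At 30% and 40% it is 0.08 and 0.01. These figures take the same risk in all arms; if treatment works, the treated arms have fewer cases still.

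**2. Precision.** The detectable standardised difference is approximately (1.960 + 0.842) × √(2/n).

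| Women per arm | Detectable difference (SD) |
|---|---|
| 16 (all randomised) | 0.99 |
| 6.4 (40%) | 1.57 |
| 4.8 (30%) | 1.81 |
| 3.2 (20%) | 2.21 |

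The normal approximation is optimistic at such sizes. The 0.99 is a best case, because women with pregestational diabetes would be left out and some values will be missing.

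**3. Uniform benefit.** Suppose treatment lowers glucose by *d* in every woman. The control mean among women with GDM is φ(c)/*p*. The treated mean is φ(c + d)/P(Z > c + d) − d.

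- *p* = 0.20, *d* = 0.50: control 1.400; treated 1.305 (GDM risk falls to 9.0%). Difference −0.09 SD.
- *p* = 0.40, *d* = 0.50: control 0.966; treated 0.831 (GDM risk falls to 22.6%). Difference −0.13 SD.
- *d* = 0.25: difference −0.05 to −0.07 SD over the same range of *p*.

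The true effect is −0.50 or −0.25 SD. The direction is kept, but most of the effect disappears.

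**4. Selective prevention of mild cases.** Suppose half of the women between *c* and *c* + 0.5 are moved to just below the cut-off (*c* − 0.1) and nobody else changes. At *p* = 0.20 the treated GDM risk is 14.5% and the mean among women with GDM is 1.525, against 1.400 in control: +0.13 SD, apparently worse. At 30% and 40% the difference is also +0.13 SD. Across all women the effect is slightly favourable, −0.02 to −0.03 SD.

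**5. Fit with the analysis rule.** Women with GDM can be grouped by allocated arm. The set analysed is still chosen by an event that allocation may change, so the comparison lacks what an intention-to-treat analysis is meant to protect.

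**The case against.** The strongest reply is that this is one secondary outcome in a 48-woman feasibility trial with no power calculation. A bias of about 0.13 SD is small beside a detectable difference of 1.6 to 2.2 SD, so imprecision is the practical limit here. The article states no test specific to this outcome, and it also plans descriptive summaries. Glycemic control in women with GDM is clinically meaningful as a description. All of this stands and limits the severity. It does not make the comparison randomised, and the bias does not shrink as the sample grows.

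Three stronger readings are tempting and are not supported.

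- A reader might infer that the oral glucose tolerance test values are wasted. They are not: the test determines the GDM outcome. What the article lacks is a continuous use of them, and since its list is open and the full list is in the registry, their absence from every outcome cannot be claimed.
- A reader might infer that all 48 women will have the test for this purpose. Outcome Assessment states no restriction, but women with pregestational type 2 diabetes are eligible, and a test meant to diagnose GDM cannot be assumed for them.
- A reader might infer that an effective therapy would look harmful. That needs selective prevention of mild cases; a uniform benefit is attenuated, not reversed.

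**Conclusion.** The point holds for the subgroup definition. The outcome is conditioned on a post-randomisation event that is itself a primary outcome and that the protocol expects treatment to reduce. A between-arm comparison within it is not protected by randomisation and does not fit the stated intention-to-treat principle. It would rest on about 3 to 6 women per arm, and it can hide most of a true benefit or, under selective prevention, reverse its sign. These sizes depend on assumed GDM risks of 20% to 40% and a one-variable normal model, neither of which comes from the article; the conditioning problem itself depends on neither. The feasibility conclusions and the GDM comparison are unaffected.

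**What to change.** Report glycemic control in women who develop GDM descriptively by arm, with the number of women contributing, and no between-arm test or P value.

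Add a comparison of the 28-week fasting, 1-hour and 2-hour glucose values as continuous outcomes in all randomised women without pregestational diabetes. Adjust for the minimization factors (previous preeclampsia, previous GDM, BMI ≥35) and give estimates with 95% CIs. Leaving out women with pregestational diabetes uses a baseline characteristic, so the randomised comparison is preserved.

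The cost is moderate. The samples are already planned, so no new data are needed. The comparison is, however, a late addition to the outcome set of an open-label trial whose last participant was recruited in December 2022, so it must be declared as added and exploratory, unless the registry already lists it. Women diagnosed with GDM early may not have the 28-week test. Their values would be missing for a reason related to glucose, so the handling of these missing values must be stated in advance.

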**Results:**

The trial commenced on September 30, 2019. The trial is ongoing as of August 6, 2024.

**Conclusions:**

The trial intends to contribute to the growing evidence base to support the need for the identification and treatment of OSA occurring during pregnancy and to assess the feasibility of the study protocol. This will be the first trial to compare the early initiation of CPAP (auto-titrating and fixed pressure) and positional therapy in pregnant women from early gestation, providing alternative therapies for the treatment of OSA in this important population.

**Trial Registration:**

Australian New Zealand Clinical Trials Registry ACTRN12619001530112; https://tinyurl.com/yctdzs4u

**International Registered Report Identifier (IRRID):**

DERR1-10.2196/51434

## Introduction

During pregnancy, physiological changes, including upper airway edema and hormone-related upper airway pressure changes, predispose women to sleep-disordered breathing (SDB) [1]. The prevalence of obstructive sleep apnea (OSA) in pregnancy increases from 3.6% in early pregnancy to 8.3% in midpregnancy and is associated with an independent risk of gestational diabetes mellitus (GDM), preeclampsia, and hypertensive disorders of pregnancy (HDP) [2]. In addition, emerging evidence suggests that the presence of SDB before pregnancy may place women at an increased risk of developing GDM [3]. Supine sleeping in late pregnancy is associated with an increased risk of stillbirth [4], and supine sleep avoidance is recommended from the 28-week gestation period [5].

Treatment options for OSA in non-pregnant adults include continuous positive airway pressure (CPAP), weight loss, positional therapy, mandibular advancement splints, surgery (both upper airway and bariatric), and pharmacological therapies, though not all are suitable for use in pregnant populations. CPAP and positional therapies reduce the occurrence of OSA by reducing the occlusion of the upper airway through pneumatic splinting [6] and repositioning the sleeping persons to reduce collapsibility of the airway [7,8], respectively. Within nonpregnant populations, longer duration CPAP compliance (more than 7 hours) was associated with a reduction in hemoglobin A_1c_ by 1% when CPAP was used for more than 85% of the rapid eye movement stage of sleep during the night [9]. Improvements in blood pressure control have been demonstrated in nonpregnant patients with OSA [10,11], and a small benefit in 24-hour diastolic blood pressure in patients using fixed pressure CPAP compared with auto-titrating CPAP has been reported [12].

In pregnancy, CPAP is recommended as the first line of treatment for OSA [13,14], although alternatives to CPAP may be beneficial but require clinical trials to investigate their utility [14]. In pregnant populations, many studies investigating CPAP treatment have used small sample sizes [15] or initiated therapy in later gestation periods. An early study of 12 pregnant women with OSA at risk of preeclampsia demonstrated no improvement in clinical maternal outcomes [16]; likewise, CPAP failed to demonstrate improvements in glucose levels in obese pregnant women with 2 weeks of CPAP use between 24- and 34-week gestation periods, although compliant use of CPAP in this study demonstrated an improvement in insulin secretion and sensitivity [17]. There are, however, some benefits reported in the literature; a single night of CPAP in a study of 10 pregnant women with preeclampsia and coexisting obesity demonstrated improvements in fetal movements [18], and an improvement in blood pressure control both during sleep and wake was reported in a small study of 7 women, resulting in down titration of antihypertensive medication [19].

Compliant use of CPAP remains a challenge, and in some patients, it may be dependent on clinical support mechanisms, with pre- and postacclimatization phase support improving therapy compliance [20]. Gender-based differences in CPAP compliance have been demonstrated in a large study of nearly 800,000 CPAP users, where women aged 18-30 had the lowest CPAP compliance (51.3%) and were most likely to cease therapy [21]. Barriers to compliant CPAP therapy in pregnant women with OSA are relatively unknown though targeted supports, which have demonstrated improvements in maternal medication compliance, may be beneficial [22]. A recent randomized controlled trial assessed blood pressure outcomes in 340 high-risk pregnant women recruited predominantly during the first trimester, allocated to CPAP or no treatment (control). Despite a mean CPAP compliance of 2.5 hours nightly, and an overall compliance (≥ 4 hours nightly) of 32.7% of participants randomized to CPAP, this reported reductions in diastolic blood pressure and preeclampsia rates [23]. This study additionally presents data on CPAP side effects, and despite rhinitis, mask difficulties, and pressure intolerance reported, there was no significant difference in the reporting of these symptoms between compliant and noncompliant participants, indicating the possibility that these side effects are not barriers to treatment in this special population.

CPAP devices are available in fixed and auto-titrating options and in nonpregnant OSA patients, patient preference has demonstrated mixed results [24,25], although data are lacking in pregnant populations. Furthermore, evidence of the efficacy of auto-titrating devices through gestation advancement is limited, and despite the availability of auto-titrating devices that attempt to target flow-limited breathing using reduced air pressure in premenopausal women [26], their utility in pregnancy is unknown.

Positional therapy is less effective at reducing apnea-hypopnea index (AHI) and nocturnal oxygen desaturation [7,27] but is effective at reducing supine sleep time [7], which is associated with the worsening of OSA [8]. Positional therapy (PT) in pregnancy is hypothesized to impact outcomes by two potentially independent pathways: first, by addressing SDB, which is typically worse in the supine position, and second, by minimizing compression of the vena cava by the gravid uterus, which may reduce fatal blood flow. A feasibility study using a back-worn positional therapy band for a single night in healthy pregnant women at 32- to 38-week gestation periods showed improvement in maternal oxygenation and reduced fetal heart rate decelerations compared with the controlled night [28].

Given placentation completes around 16-week gestation period, the timing of OSA treatment intervention may be particularly important, as data demonstrates significant benefits of time-specific interventions in pregnancy, for example, aspirin is generally beneficial in preventing preeclampsia if commenced before 16-week gestation period [29]. We thus outline a protocol to determine the feasibility of a parallel group, individually randomized, controlled, open-label trial comparing CPAP or PT to usual care (control). Commencement of therapy by the 16th week of gestation has been chosen to reduce exposure to intermittent hypoxia on the developing placental function during early pregnancy and to establish early compliance to treatment. The use of fixed pressure CPAP after auto-titration of pressure in this trial was determined by factors including access to trial equipment, cost, and absence of evidence of the superiority of auto-titrating over fixed pressure CPAP in pregnancy. This trial aims to determine the feasibility of conducting a larger trial and to obtain preliminary recruitment and efficacy data that may be used to design and power a larger trial. This study may be of interest to others conducting sleep therapy intervention studies in pregnant women.

